## Abstract

**Background::**

Adhesive small bowel obstruction (ASBO) is one of the most common complications and is a major cause of re-admission after intra-abdominal surgery. The initial management of patients with ASBO is nonoperative treatment such as nil per os and decompression using a nasogastric tube. However, the ideal management of ASBO remains controversial.

**Methods::**

This study will be a prospective, single-center, double-blind randomized controlled trial. Ninety two participants diagnosed with ASBO will be randomly assigned to either the verum or the sham laser acupuncture (SLA) group in a 1:1 ratio. All participants will undergo laser acupuncture (LA) or SLA once a day on 6 acupoints (LI4, PC6, ST25, ST36, CV4 and CV12) for 6 consecutive days after enrollment. The primary outcome measure will be the success rate of conservative treatment for ASBO. Secondary outcomes will be time to oral intake and length of hospital stay. The serum levels of lipase, amylase, cortisol, motilin, ghrelin, and intestinal fatty acid binding protein (I-FABP) will also be measured before intervention, on day 4, and on the day of discharge, respectively. Data will be analyzed by Chi-Squared test or t test between 2 groups.

**Objectives::**

The aim of this protocol is to investigate the clinical efficacy of LA on ASBO.

**Trial registration::**

ClinicalTrials.gov Identifier: NCT04318821. Registered on 24 March 2020.

## Introduction

1

Adhesive small bowel obstruction (ASBO) is one of the most common complications and is a major cause of admission after intra-abdominal surgery. The incidence of ASBO following all types of abdominal surgery is 2.4%.^[1]^ Less commonly, the adhesions may form as a result of inflammatory conditions, intraperitoneal infection or abdominal trauma.^[2]^ Definitive confirmation of ASBO is made during operative treatment. In the initial 72 hours, nonoperative management for ASBO patients is appropriate unless there are signs of peritonitis, strangulation, or bowel ischemia.^[3,4]^ Approximately 70% to 90% of patients with ASBO respond to nonoperative treatment.^[3]^ Surgery intervention for adhesions should be considered for patients with repeated ASBO or unsuccessful conservative treatment, as any delay in surgical intervention is associated with higher mortality and complication rates if nonoperative management is unsuccessful after 3 days.^[4]^ To date, the ideal management of ASBO remains disputed. Therefore, the development of a new feasible treatment to increase the likelihood of successful nonoperative treatment and reduce the recurrence of ASBO is of great clinical significance.

Laser acupuncture (LA) combines the characteristics of traditional metal-needle acupuncture and low-level laser therapy. While acupuncture has been reported to promote the recovery time of postoperative ileus in patients with colorectal cancer,^[5]^ the application of LA for ASBO is very rare, and only 1 pre-clinical study has shown low level laser therapy to be effective in preventing intra-abdominal adhesions in rabbits without compromising the strength and healing of the abdominal wall.^[6]^ We assume that conventional treatment combined with LA will be effective for reducing the need for surgery through eliminating the symptoms of ASBO. The major aim of this study is to investigate the clinical benefits and the adverse events of LA in patients with ASBO. Furthermore, we want to explore the short-term effects or changes in several serum biomarkers associated with ASBO, including serum lipase, amylase, cortisol, motilin, ghrelin, and intestinal fatty acid binding protein (I-FABP). These serum biomarkers are associated with bowel movements and injuries, as explained in the discussion section.

## Methods/design

2

### Ethics approval

2.1

This protocol has been reviewed and approved by the Human Ethics Committee of the Chang Gung Medical Foundation Institutional Review Board (IRB no. 201901450A3; version 1 on October 28, 2019). The protocol identification number at https://clinicaltrials.gov is NCT04318821. This study will be conducted in accordance with the principles of the Declaration of Helsinki. Both verbal and written forms of detailed information about the trial will be provided before participation by trauma surgery physicians at Kaohsiung Chang Gung Memorial Hospital (KCGMH). All participants will provide voluntarily signed informed consent that has been approved by the ethics committee prior to enrollment. Personal information about potential and enrolled participants will be collected, shared, and maintained in an independent and secure storage space in order to protect confidentiality before, during, and after the trial. We will present the final results and submit them for publication in peer-reviewed journals. [name] and [name] will have access to the final trial dataset and disclosure of contractual agreements that limit such access for investigators.

### Study design

2.2

This prospective, single-center, randomized, double-blind, controlled trial began at the Department of Trauma Surgery at the Kaohsiung Chang Gung Memorial Hospital (KCGMH) in South Taiwan from March 2020 and will continue until February 2022. Ninety two participants will be randomly assigned to the experimental group (LA plus conventional treatment, n = 46) or control group (sham LA [SLA] plus conventional treatment, n = 46). All participants will receive LA or sham LA after enrollment, once daily for 6 days, during hospitalization. The study design according to Consolidated Standards of Reporting Trials (CONSORT) 2010 is depicted in Figure 1.

**Figure 1 F1:**
[figure not shown]
The flowchart of the trial.

### Participants

2.3

The information of the trial will be provided by Trauma Surgery physicians at KCGMH. Participants’ eligibility in the study will be assessed by trauma surgeons. Written informed consents will be obtained for all participating patients before randomization. All patients with ASBO will be managed from the time of admission by the trauma surgery team, who have no information about the allocation results.

The study inclusion criteria are as follows:

1.patients aged 20 to 80 years;2.patients with clinical symptoms and signs of mechanical obstruction, such as intermittent colicky abdominal pain, nausea with or without vomiting, abdominal distension, and absence of stools; and the results of plain abdominal radiographs performed with the patient upright or CT revealing dilated loops of the small intestine;3.consent to participate in the study.

Participants with the following conditions will be excluded:

1.clear non-adhesive etiology of small bowel obstruction (e.g., tumor, hernia);2.emergency surgical intervention before enrollment;3.pregnancy;4.local skin infection on the acupoints or limb amputees;5.unwillingness to provide informed consent.

Participants will be dropped from the trial under the following conditions:

1.unstable vital signs and/or need for first aid during study period;2.deterioration of clinical condition and determination of unsuitability to continue this study by medical staff;3.voluntary decision by participants to withdraw from the trial at any time.

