### Sample size, blinding, and randomization

2.4

As no related studies on the effects of acupuncture or laser acupuncture for the treatment of ASBO have been published, we determined the necessary sample size based on a previous study of the effects of sesame oil on ASBO.^[7]^ The surgical rate was 12.9% in the experimental group and 48.5% in the control group. Anticipating a power of 95% (1-β = 0.95), statistical significance (α = 0.05) of 95%, and a dropout rate of 10%, a total of 92 participants will be required in this study, according to G∗power analysis.

All the participants will be informed that they will receive laser acupuncture in addition to the conventional treatment and assess the efficacy of laser acupuncture for ASBO. The laser acupuncture devices used in the LA and SLA groups will have the same appearance. The difference will be that no energy will be output during the intervention in the SLA group. The participants will be unable to recognize whether they are being treated or not because laser acupuncture involves low-intensity, non-thermal laser irradiation that it is hard to detect. Participants will be randomly allocated to either the LA or the SLA group in a 1:1 ratio using computer-generated random numbers. Randomization will be performed by an independent researcher with no involvement in the inclusion and exclusion process, treatment, or outcome assessments.

The participants, outcome assessors, and data analysts will be blinded to the allocation of interventions using labels A and B for the 2 groups until the trial is completed.

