### Interventions

2.5

All participants will receive conventional treatment, including nonoperative managements, initially, and perhaps further surgical intervention if indicated according to the Bologna guidelines of ASBO^[3]^ and the trauma gastrointestinal surgeons’ expertise. Therapeutic efficacy will be defined by the appearance of flatus/defecation, radiological improvement, relief of abdominal symptoms, decreased drainage volume of nasogastric decompression, disappearance of air-fluid levels, or reduced gas and fluid in bowel loops. The nasogastric tube will be removed when the drainage output decreases to less than 200 ml per day or flatus/defecation occurs. A liquid diet will be administered gradually, typically followed by a soft diet and then solid food as tolerated. Patients will be discharged when solid food is well tolerated. If the patient presents no improvement and progresses into strangulation, peritonitis, or bowel ischemia, surgery will be recommended.^[3]^

The participants in each group will undergo real LA or sham LA treatment once daily for 6 days, using a gallium aluminum arsenide Laser Pen (maximal power, 150 mW; wavelength, 810 nm; area of probe, 0.03 cm^2^; power density, 5 W/cm^2^; pulsed wave; and Bahr frequencies (B1: 599.5 Hz, B2: 1199 Hz, B3: 2398 Hz, B4: 4776 Hz, B5: 9552 Hz, B6: 19,104 Hz, and B7: 38,208 Hz]; RJ-Laser, Reimers & Janssen GmbH, Waldkirch, Germany). We will use the same acupoints and manipulations in both groups. The participants in the control group will receive SLA treatment without any laser output (no stimulation), while the participants in the experimental group will sequentially receive 0.375 J of energy at each of the following acupoints: LI4 (Hegu, B3), PC6 (Neiguan, B3), ST25 (Tianshu, B3), ST36 (Zusanli, B2), CV4 (Guanyuan), and CV12 (Zhongwan, B3) (Fig. 2). The laser treatment will be applied to each point for 5 seconds to deliver a total treatment dose of 4.5 J/cm^2^. All acupoints have been selected and localized according to the WHO Standardized Acupuncture Point Location guidelines.^[8]^ In all the subjects, the laser application will be performed by the same experienced physician, who has sufficient training and is a licensed Chinese medicine practitioner in Taiwan.

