### Outcome measurements

2.6

The primary outcome measurement will be the success of conservative treatment, which is defined as no need for nasogastric tube decompression or operative intervention. Secondary outcome measurements will include time to oral intake, length of hospital stay, and changes in serum amylase, lipase, cortisol, motilin, ghrelin, and I-FABP levels, which will be checked before the intervention, on the fourth day, and on the day of discharge, respectively. The reasons why participants are unable to complete the follow-up treatments or withdraw from the study, such as adverse events, suboptimal response to therapy, surgical intervention for ASBO, or refusal to receive intervention, will be recorded.

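### The rule that drops deteriorating patients from the trial overlaps with failure of the primary outcome, so failures can be removed because of their outcome

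*Protocol article*

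**What the plan says.** All of this is in the protocol article.

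- **Participants (2.3)** opens its list of drop conditions with "Participants will be dropped from the trial under the following conditions". The first is "unstable vital signs and/or need for first aid during study period". The second is "deterioration of clinical condition and determination of unsuitability to continue this study by medical staff". The third is voluntary withdrawal.
- **Outcome measurements (2.6)** defines the primary outcome as "success of conservative treatment, which is defined as no need for nasogastric tube decompression or operative intervention". An operation is therefore a failure.
- **Interventions (2.5)** gives the route to an operation: "If the patient presents no improvement and progresses into strangulation, peritonitis, or bowel ischemia, surgery will be recommended".
- **Outcome measurements (2.6)** also covers patients who cannot complete treatment or who withdraw. Their reasons, "such as adverse events, suboptimal response to therapy, surgical intervention for ASBO, or refusal to receive intervention, will be recorded". One list serves both for stopping treatment and for leaving the study.
- **Sample size (2.4)** plans on these rates: "The surgical rate was 12.9% in the experimental group and 48.5% in the control group". It adds "a dropout rate of 10" per cent and arrives at 92 participants.

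**The concern.** A patient whose obstruction progresses to strangulation, peritonitis or ischemia is deteriorating, and is also the patient for whom surgery is recommended. The same clinical course can therefore meet a condition for leaving the trial and produce a primary failure. If the patient is dropped before the operation is recorded as the outcome, a failure disappears from both numerator and denominator.

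That loss depends on the outcome. If it is equal across arms, both failure rates and their difference are understated and power is lost. If it differs between arms, it can create a difference where none exists. The patients who remain are no longer the randomised groups. The second condition also turns on staff judgement, so whether a given failure stays in is partly discretionary.

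**Working it through.** **1. Reproducing the planned size.** Inputs from 2.4: p1 = 0.129, p2 = 0.485, alpha 0.05 (taken as two-sided), power 0.95, dropout 10%. With the mean rate p̄ = 0.307 and the pooled formula without continuity correction,

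n = [1.960·√(2·p̄(1−p̄)) + 1.645·√(p1(1−p1) + p2(1−p2))]² / (p2−p1)² = 40.6, so 41 per arm.

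Then 41/0.90 = 45.6, so 46 per arm and 92 in total. This matches the article. The inflation from 82 to 92 treats a dropout as contributing no primary outcome.

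**2. Operations expected on the planning rates.** 46 × 0.129 = 5.9 and 46 × 0.485 = 22.3, together 28.2 of 92, or 30.7%. The dropout allowance is 10%. With no other dropouts, it would be used up once 0.10/0.307 = 33% of operated patients were lost.

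**3. Equal removal of a share f of failures in both arms.** The article gives no value for f, so a range is assumed. The planning rates are surgical rates, so surgery stands in for failure here.

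- Observed failure rate: q = p(1−f)/(1−pf).
- Expected patients left per arm: 46(1−pf).
- Example, f = 0.50: 0.0645/0.9355 = 6.9% and 0.2425/0.7575 = 32.0%.

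Power is by exact enumeration of the two-sided uncorrected chi-squared test.

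| f | LA rate | SLA rate | Difference (points) | Patients left (LA, SLA) | Power |
|---|---|---|---|---|---|
| 0 | 12.9% | 48.5% | 35.6 | 46, 46 | 97% |
| 0.25 | 10.0% | 41.4% | 31.4 | 44.5, 40.4 | 94% |
| 0.50 | 6.9% | 32.0% | 25.1 | 43.0, 34.8 | 84% |
| 0.75 | 3.6% | 19.1% | 15.5 | 41.5, 29.3 | 60% |

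The normal approximation gives 93%, 82% and 57% for the last three rows.

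**4. No true effect.** Assume a 30% failure rate in both arms and 46 per arm, with the same test.

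- Equal removal of 25%, 50% or 75%: type I error about 5% each time.
- Removal of 50% in one arm and 25% in the other: about 11%.

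**The case against.** The strongest reply is that the decisive step is inferred. The article nowhere says that a dropped patient leaves the primary analysis or that the outcome goes uncollected. The outcome definition makes surgery a failure, and Interventions treats surgery as part of the planned course. A full protocol or SAP may define an intention-to-treat set. This stands in part: a reader might infer that the plan excludes operated patients from the primary comparison, and the text does not support that. The missing analysis set is also not the point. What remains is a stated rule that takes patients out of the trial. An analysis set cannot restore an outcome that was never collected.

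Four further points have weight.

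- The list of reasons in 2.6 can be read as reasons for stopping laser sessions, which suits an operated patient. That reading is fair there. The drop rule in 2.3 refers to the trial and does not invite it.
- The second drop condition needs both deterioration and a judgement of unsuitability, so overlap with failure is partial and of unknown size.
- The 10% allowance is not said to cover failures. A reader might infer that it contradicts the planned surgical rates, but that follows only if many operated patients leave as dropouts. Setting 10% beside about 31% could equally mean that the authors did not regard surgery as dropout.
- A reader might infer severe false-positive inflation. Removing 75% of failures in one arm and 25% in the other would give a type I error of about 40%. Nothing in the article supports such an imbalance. The surgical team has no allocation information (2.3), and participants, assessors and analysts are blinded (2.4).

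**Conclusion.** The point holds in a limited form. As written, the drop rule can remove primary failures in a way that depends on the outcome, and 2.6 does not separate stopping treatment from leaving the trial. The main consequence is an understated difference and lost power: modest if a quarter of failures go (94%), serious if three quarters go (60%). False-positive inflation is a secondary risk. It needs unequal removal, which the blinding makes less likely, and reaches about 11% in the 50% against 25% scenario.

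These sizes rest on assumed removal shares, on surgery standing in for failure, and on dropped patients contributing no outcome. The article settles none of these. It matters because the events at risk are those that the primary outcome counts.

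**What to change.** - In 2.3, replace removal from the trial for instability or deterioration with discontinuation of the study laser sessions, with follow-up to discharge for the primary outcome. In 2.6, record reasons for stopping laser separately from reasons for leaving the study.
- Analyse all randomised patients in their assigned arm.
- Count any operation, and any other event in the 2.6 failure definition, as a failure whatever the reason for discontinuation.
- Limit dropout to withdrawal of consent with unknown outcome, and add a best-case and worst-case sensitivity analysis for those patients.
- Deterioration or instability without surgery goes beyond the 2.6 definition. Treat it as failure in a sensitivity analysis only.

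The cost is a protocol amendment and matching SAP wording. Patients are in hospital and operations are in the chart, so no new visits are needed. The change concerns outcome collection and counting only; no clinical management rule needs to change.

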### Sample size, blinding, and randomization

2.4

As no related studies on the effects of acupuncture or laser acupuncture for the treatment of ASBO have been published, we determined the necessary sample size based on a previous study of the effects of sesame oil on ASBO.^[7]^ The surgical rate was 12.9% in the experimental group and 48.5% in the control group. Anticipating a power of 95% (1-β = 0.95), statistical significance (α = 0.05) of 95%, and a dropout rate of 10%, a total of 92 participants will be required in this study, according to G∗power analysis.

All the participants will be informed that they will receive laser acupuncture in addition to the conventional treatment and assess the efficacy of laser acupuncture for ASBO. The laser acupuncture devices used in the LA and SLA groups will have the same appearance. The difference will be that no energy will be output during the intervention in the SLA group. The participants will be unable to recognize whether they are being treated or not because laser acupuncture involves low-intensity, non-thermal laser irradiation that it is hard to detect. Participants will be randomly allocated to either the LA or the SLA group in a 1:1 ratio using computer-generated random numbers. Randomization will be performed by an independent researcher with no involvement in the inclusion and exclusion process, treatment, or outcome assessments.

The participants, outcome assessors, and data analysts will be blinded to the allocation of interventions using labels A and B for the 2 groups until the trial is completed.

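### The 95% power rests on a 48.5% control surgery rate that the protocol's own background figure does not support, and it is not power for the composite primary outcome

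*Protocol article*

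**What the plan says.** Section 2.4 of the protocol article explains that no acupuncture study in adhesive small bowel obstruction (ASBO) was available, and so "we determined the necessary sample size based on a previous study of the effects of sesame oil on ASBO". The planning rates are given as "The surgical rate was 12.9% in the experimental group and 48.5% in the control group". With 95% power, α = 0.05 and 10% dropout, the section concludes that "a total of 92 participants will be required in this study", allocated 1:1.

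The Introduction gives a different picture of the same condition: "Approximately 70% to 90% of patients with ASBO respond to nonoperative treatment".

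Section 2.6 defines primary success as needing neither nasogastric decompression nor an operation. No expected failure rate for that composite appears anywhere in the article. Section 2.7 names the chi-squared test for categorical data.

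**The concern.** The planning control rate is 1.6 times the upper end of the range implied by the Introduction (48.5/30) and almost five times the lower end (48.5/10). Nothing in the eligibility criteria (section 2.3) selects patients more likely to need surgery; those who had emergency surgery before enrollment are excluded. Control patients are managed under the Bologna guidelines (section 2.5, reference 3), the same reference that the Introduction cites for the 70% to 90%. The protocol does not say why its controls should need surgery so much more often.

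The sizing endpoint is also not the primary endpoint. Section 2.4 uses surgery; section 2.6 uses surgery or nasogastric decompression.

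At stake is how the stated 95% is read. It tells the reader that a worthwhile effect would very probably be detected. If that depends on a control rate the protocol's own background does not support, and on an endpoint narrower than the primary one, the reassurance is not earned.

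**Working it through.** **Inputs.** From section 2.4: p₁ = 0.129 (experimental), p₂ = 0.485 (control), α = 0.05, power 0.95, dropout 10%, N = 92, ratio 1:1. Sidedness is not stated; two-sided reproduces the figure. From the Introduction: 70% to 90% respond, so failure is 100 − 90 = 10% to 100 − 70 = 30%.

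**Step 1: the plan's own figure.** Pooled two-sided formula without continuity correction, with p̄ = (0.129 + 0.485)/2 = 0.307:

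n = [1.960·√(2·0.307·0.693) + 1.645·√(0.129·0.871 + 0.485·0.515)]² / 0.356²
= [1.960·0.6523 + 1.645·0.6018]² / 0.1267
= 5.145/0.1267 = 40.6, so 41 per arm and 82 in total.

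Dropout: 82/0.9 = 91.1, so 92. This matches. Exact enumeration of the uncorrected chi-squared test at 41 per arm gives 95.5% power. The arithmetic is sound.

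**Step 2: planned effect sizes.** Difference 48.5 − 12.9 = 35.6 points. Relative risk 0.129/0.485 = 0.266. Odds ratio (0.129/0.871)/(0.485/0.515) = 0.157.

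**Step 3: the largest possible difference on the Introduction's range.** If control surgery is 10% to 30%, abolishing it removes 10 to 30 points, less than 35.6.

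**Step 4: power for surgery on that range.** The LA-arm rate at these control rates is not in the document, so several assumptions are shown. Exact enumeration, uncorrected chi-squared, two-sided 0.05, 41 evaluable per arm:

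| Assumed LA effect | Control 30% | Control 20% | Control 10% |
|---|---|---|---|
| Same relative risk, 0.266 (LA 8.0%, 5.3%, 2.7%) | 76% | 56% | 29% |
| Same odds ratio, 0.157 (LA 6.3%, 3.8%, 1.7%) | 84% | 69% | 38% |
| Surgery halved | 38% | 25% | 15% |
| LA rate kept at 12.9% | 48% | 14% | no benefit |
| No surgery under LA | about 100% | 98% | 60% |

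The normal-approximation formula gives slightly lower values for the same relative risk: 73%, 52% and 27%. With no dropout (46 per arm), exact power for the same relative risk is 81%, 61% and 33%.

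**Step 5: what would keep 95%.** By the same enumeration, LA would have to bring surgery to about 3% from a 30% control rate, or below 0.5% from a 20% rate. From 10%, 95% cannot be reached.

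**Step 6: the primary outcome.** Composite failure can be no rarer than surgery and may be much commoner, because the Abstract and Discussion list nasogastric decompression as part of initial nonoperative care. As illustration only, with assumed control failure of 40% or 60%: the planned relative risk gives 89% or 99%, and a halving gives 51% or 81%. Both the composite control rate and the LA effect on it are unknown, so no single power follows from the document.

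**The case against.** The case for the protocol has four parts.

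- **The source is disclosed and the sum is right.** With no acupuncture data, borrowing from another ASBO trial is a reasonable start. This stands: the fault is an unreconciled planning input, not a calculation error.
- **48.5% was reported in a cited control group, and 70% to 90% is an approximate background range.** A reader might infer that the planned 35.6-point difference simply cannot occur. The documents do not support that. It is out of reach only if the 10% to 30% range applies to surgery in this trial, and treating non-response as surgery is itself an inference. The high rate is unjustified, not impossible.
- **A difference below 35.6 points does not by itself mean low power.** This also stands: a fall from 30% or 20% to zero would still give about 100% or 98%. The low figures need an assumption about the LA rate as well. However, every assumption as strong as the planned effect or weaker gives at most 84%, and to keep 95% surgery must almost disappear.
- **All the figures are for surgery, while the primary outcome is wider.** A reader might take 29% to 76% as the trial's real power. It is not: power for the composite could be higher or lower. This limits the criticism, but it does not rescue the 95%, which was computed for surgery too.

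How the result will be reported, and how a non-significant result will be worded, may properly be left to the analysis plan and is not part of this point.

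**Conclusion.** The point holds in conditional form. The sample size of 92 is correctly computed from its inputs, but the control surgery rate behind it lies well above the range in the protocol's own Introduction, without explanation. On that range, surgery-only power with 41 evaluable per arm runs from 15% to 84% across the three effect assumptions (same relative risk, same odds ratio, halving), against the stated 95%. This rests on failure of nonoperative treatment being read as surgery, a two-sided uncorrected chi-squared test and 10% dropout. Separately, the 95% is unsupported for the primary outcome in section 2.6, because it was derived for a narrower endpoint and no composite failure rate is given. The size and direction of that second discrepancy cannot be determined from the document.

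**What to change.** Keep N at 92 and revise section 2.4 as follows.

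1. State that 92 patients give 95% power for the surgical rate only, and only if surgery is 48.5% in controls and 12.9% with LA.
2. Add the surgery-only power at the Introduction's 10% to 30%: about 29% to 76% at relative risk 0.266, 38% to 84% at odds ratio 0.157, and 15% to 38% for a halving. Label these as not being power for the primary outcome.
3. Either justify 48.5% for this population against the Introduction's figure, or state the power for the composite primary outcome using an explicit assumed failure rate, with a range.

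The cost is text only, with no additional patients. The downside is that the stated power becomes less favourable. For scale, holding 95% for surgery at the planned relative risk with 10% dropout would need 178, 292 or 632 patients at control rates of 30%, 20% or 10% (formula in step 1), which is why the proposal is to restate the claim rather than enlarge the trial.

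### The protocol says every participant will be told they will receive laser acupuncture, but by design half (46 of 92) receive a device with no output, so the sentence must be corrected and checked against the approved information sheet.

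*Protocol article*

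**What the plan says.** Section 2.4 (Sample size, blinding, and randomization) describes what participants are told: "All the participants will be informed that they will receive laser acupuncture in addition to the conventional treatment". The sentence then runs on, in broken grammar, to assessing the efficacy of laser acupuncture.

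The same section describes the control device: "no energy will be output during the intervention in the SLA group". It sets the allocation: "Participants will be randomly allocated to either the LA or the SLA group in a 1:1 ratio". Section 2.5 (Interventions) repeats the content of the control arm: "The participants in the control group will receive SLA treatment without any laser output (no stimulation". Section 2.2 (Study design) gives the arm size: "control group (sham LA [SLA] plus conventional treatment, n = 46", out of 92.

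On consent, Section 2.1 (Ethics approval) says: "Both verbal and written forms of detailed information about the trial will be provided before participation". It adds that participants give "voluntarily signed informed consent that has been approved by the ethics committee prior to enrollment". Section 2.3 (Participants) fixes the timing: "Written informed consents will be obtained for all participating patients before randomization".

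No section says that participants are told a sham arm exists or that they might be assigned to it.

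**The concern.** The article does more than leave consent wording to another document. It states what all participants will hear, and that statement contradicts the design set out in the same section. Someone who will be randomised 1:1 to an active or an inactive device cannot truthfully be told, before randomisation, that they will receive the active treatment.

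What is at stake is whether consent is informed. The setting makes this more than a formality. Participants have an acute condition, and the Introduction associates delayed surgery with higher mortality and more complications when nonoperative management has not succeeded after 3 days. Patients in that position should know that the added treatment may be inactive.

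The blinding does not need the statement. Section 2.4 rests the blinding on devices of the same appearance, on irradiation that is hard to feel, and on group labels A and B kept until the trial is completed. Those measures conceal which treatment a participant has. They do not depend on participants believing that everyone gets the active one.

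**Working it through.** **Inputs**

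| Item | Value | Where |
|---|---|---|
| What all participants are told | They will receive laser acupuncture | Section 2.4 |
| Output of the control device | Zero | Sections 2.4 and 2.5 |
| Allocation ratio | 1:1 | Section 2.4 |
| Control arm / total | 46 / 92 | Section 2.2 |
| Timing of consent | Before randomisation | Section 2.3 |
| Content of the consent form | Not shown | Section 2.1 says only that it was approved |

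**Step 1: the plan's own figure.** The 46 per arm can be reproduced from the assumptions in Section 2.4: surgical rates 12.9% and 48.5%, power 95%, α = 0.05 and 10% dropout. Sidedness is not stated; two-sided is assumed. With pooled variance and no continuity correction, p̄ = (0.129 + 0.485)/2 = 0.307, and

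n per arm = [1.960·√(2·0.307·0.693) + 1.645·√(0.129·0.871 + 0.485·0.515)]² / (0.485 − 0.129)²

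= [1.960·0.6523 + 1.645·0.6018]² / 0.1267 ≈ 5.145 / 0.1267 ≈ 40.6, which rounds up to 41.

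The total is 2 × 41 = 82. With dropout it is 82 / 0.9 = 91.1, which rounds up to 92, or 46 per arm. The sample size is in order, and this point does not touch it.

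**Step 2: for how many is the statement untrue?** 46 / 92 = 50%.

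**Step 3: is it true when it is made?** Consent precedes randomisation. Under 1:1 allocation, the probability of the active device at that moment is 1/2. The statement would need a probability of 1, so it is not a correct description for anyone at the time of consent. For 46 participants it remains untrue afterwards.

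**Step 4: does another section correct it?** Section 2.1 promises detailed verbal and written information but does not say what it covers. Section 2.3 gives the timing of consent only. Section 2.5 describes the sham, not what participants are told about it. Nothing withdraws or qualifies the sentence in Section 2.4, and no reason or debriefing is given for withholding the existence of a sham.

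**Step 5: does it reach the comparison between arms?** Both arms hear the same statement, so any expectation it raises is the same in both by design. On its own it does not bias the difference between arms.

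**The case against.** The strongest reply is that this is loose wording. The sentence is grammatically damaged. The article uses laser terms for both arms elsewhere: Section 2.5 has one physician perform the laser application in all subjects, and Section 2.8 monitors adverse events during laser acupuncture without separating the arms. The sentence stands in a paragraph on blinding, where its purpose may simply be that both arms are told the same thing. The article is a condensed account, and the information sheet, which an ethics committee approved, may well disclose the sham.

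Much of this stands. A reader might infer that control patients actually gave consent on a false statement. The documents do not show that, because the form is not available. A reader might also infer that sham patients would hold out longer against an operation, which would affect the primary outcome. The documents do not support that either. Section 2.5 bases surgery on a guideline, the surgeons' judgement and clinical progression; Section 2.3 keeps the managing team unaware of allocation; and no section describes how patients decide. Nor does anything in the documents suggest that the data would be unusable.

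What does not stand is the idea that nothing needs changing. If the form does disclose the sham, the protocol misreports what participants are told. If it does not, the form has the same fault. The ethics approval in Section 2.1 does not settle which, because the article does not say what the approved form discloses.

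**Conclusion.** The point holds as an inconsistency within the protocol text. Section 2.4 says that all participants will be told they will receive laser acupuncture, while the design gives 46 of 92 (50%) a device with no output. The sentence does not fit the detailed information and informed consent described in Section 2.1, and it should be corrected.

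The conclusion rests on a literal reading of the sentence and on the absence of any correction elsewhere in the article. Whether any participant was misinformed depends on the approved form and remains open. This is a consent point. It has no consequence for the sample size, the planned tests or the validity of the comparison between arms.

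**What to change.** Replace the sentence in Section 2.4 with: *Participants will be informed that they will be randomly assigned, with equal chance, to active laser acupuncture or to an inactive device of the same appearance, both in addition to conventional treatment.*

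Then check the approved information sheet against the new sentence. If it already discloses the inactive device, only the protocol wording changes. If it carries the untrue statement, amend it and re-inform the participants already enrolled; the trial began in March 2020, so there may be some.

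The cost is one protocol sentence and a document check, plus an amendment and re-information only where the sheet is at fault. The small downside is that treatment expectation may be somewhat lower, equally in both arms. The assignment stays concealed, and the sample size and analysis are unchanged.
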